**Methods/Design:**

In a RCT we will compare the ketogenic diet with usual care. Embedded in this RCT will be a trial-based and model-based economic evaluation, looking from a societal perspective at the cost-effectiveness and cost-utility of the ketogenic diet versus usual care. Fifty children and adolescents (aged 1-18) with intractable epilepsy will be screened for eligibility before randomization into the intervention or the usual care group. The primary outcome measure is the proportion of children with a 50% or more reduction in seizure frequency. Secondary outcomes include seizure severity, side effects/complaints, neurocognitive, socio-emotional functioning, and quality of life. Costs and productivity losses will be assessed continuously by a prospective diary and a retrospective questionnaire. Measurements will take place during consults at baseline, at 6 weeks and at 4 months after the baseline period, and 3, 6, 9 and 12 months follow-up after the 4 months consult.

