### Sample Size

A 50% reduction in seizure frequency is considered clinically relevant and is defined as success. Assuming a minimum detectable difference in success rate of 35% between the ketogenic diet group and usual care, and assuming that alpha = 5% and power = 80%, we need 22 children for each group. Taking dropouts into account, we need 50 children in total. A drop-out is defined as a child who drops out of the study before the first consultation with the neurologist; this is scheduled 6 weeks after initiating the KD or 6 weeks after randomization to usual care.

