### Randomization and procedure

Randomization will occur halfway through the 4 week baseline period. We will use a software package (ALEA) to support the online patient registration and randomization which will be based on the minimization method. Patients will be stratified according to age (1-6 years, 7-12 years, 13-18 years), having a PEG/tube or not, and whether the child is living at a residential centre or attends the epilepsy centre as an outpatient while she/he lives at home. In view of the nature of the treatments, blinding of the patients and researchers is not possible.

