### Analyses

#### I) Effect evaluation

Our primary (base-case) analyses will be performed according to the intention-to-treat principle, including data from all participants regardless of whether they received the intervention or not. For the analyses we will use SPSS statistical software. Respondents for whom at least 75% of the data per measurement instrument are available will be included in the analysis. Missing data on an item level will be handled using SPSS missing value regression analysis. Completely missing measurements will be handled using multiple imputation. Between-group differences in proportions (dichotomous variables) will be tested using the Chi-square test and between-group differences in means (continuous variables) will be tested using Student's t-test for independent samples. In addition, a multivariate regression analysis will be performed with the covariates of sex, age, severity of disease, duration of disease etc. The accuracy of the findings will be expressed in terms of 95% confidence intervals.

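### The primary chi-square test uses none of the three minimization factors, and the supporting regression names only age among them; adjusting for all three is a cheap gain in precision

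*Protocol article*

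**What the plan says.** All references are to the protocol article; no analysis plan is at hand.

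- **Endpoint (Abstract, Methods/Design):** "The primary outcome measure is the proportion of children with a 50% or more reduction in seizure frequency".
- **Allocation (Randomization and procedure):** minimization, with "Patients will be stratified according to age (1-6 years, 7-12 years, 13-18 years), having a PEG/tube or not", and a third factor that separates children in a residential centre from outpatients living at home.
- **Test (Analyses, I) Effect evaluation):** "Between-group differences in proportions (dichotomous variables) will be tested using the Chi-square test". No adjustment is mentioned for this test.
- **Supporting analysis (same section):** in addition, a "multivariate regression analysis will be performed with the covariates of sex, age, severity of disease, duration of disease etc". Neither the type of model nor the outcome it applies to is given.
- **Size (Sample Size):** a "minimum detectable difference in success rate of 35% between the ketogenic diet group and usual care", "assuming that alpha = 5% and power = 80"%, and hence "we need 22 children for each group". No control success rate is given.

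**The concern.** Minimization forces the arms to be alike on the chosen factors. If those factors predict response, the difference in proportions varies less from trial to trial than it would under simple randomization. The chi-square test does not know this. Its standard error still includes the outcome variation between factor levels, which the allocation has largely removed from the comparison. The test then rejects too rarely and its interval is too wide. With 22 children per arm, giving away precision that the design has already secured is a real, if modest, loss.

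The supporting regression does not clearly make this good. It is secondary, it names one of the three factors, and its open list does not fix which covariates enter.

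**Working it through.** **1. The plan's own sample size.** No control rate is stated, so one has to be assumed. The two-sided pooled formula is

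n = [1.96·√(2p̄(1−p̄)) + 0.8416·√(p0(1−p0)+p1(1−p1))]² / (p1−p0)².

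At 5% v 40%, p̄ = 0.225: [1.96·√0.34875 + 0.8416·√0.2875]² / 0.1225 = (1.157 + 0.451)² / 0.1225 = 21.1, so 22. This agrees with the article. At 10% v 45% the same formula gives 25. Other formulas also reach 22: unpooled two-sided at a 10% control rate, and one-sided pooled at 15%. A control rate of 5% is therefore one reading, not a stated input.

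**2. Cost of ignoring the factors.** Minimization was simulated with n = 44 and 1,500 trials per setting. Assumptions, none of them from the article: biased coin 0.8, equal age bands, 30% PEG/tube, 30% residential, and the same log-odds per level for each factor. The comparison is the unadjusted chi-square test against a linear model of response on treatment and the three factors, with a t reference on 44 − 6 = 38 degrees of freedom.

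Power (%), chi-square / adjusted:

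| Log-odds per level | 5% v 40% | 10% v 45% |
|---|---|---|
| 0 | 86.7 / 85.7 | 78.9 / 77.5 |
| 0.5 | 87.3 / 87.1 | 78.5 / 79.1 |
| 1.0 | 86.2 / 88.7 | 78.3 / 83.3 |
| 1.5 | 87.6 / 91.6 | 80.2 / 87.7 |

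Type I error (%), chi-square / adjusted:

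| Log-odds per level | 10% in both arms | 20% in both arms |
|---|---|---|
| 0 | 4.1 / 4.2 | 5.2 / 5.1 |
| 0.5 | 3.8 / 3.4 | 5.1 / 4.9 |
| 1.0 | 3.8 / 4.7 | 4.8 / 6.1 |
| 1.5 | 3.2 / 5.1 | 2.8 / 5.5 |

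The Monte Carlo standard error of a type I error near 5% is √(0.05·0.95/1500) = 0.6 points.

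Runs with other assumed prevalences (20% PEG/tube, 25% residential, 3,000 trials per setting, log-odds 1.0 to 1.5) agree:

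- 5% v 40%: power 87% unadjusted, 89% to 91% adjusted.
- 30-point effect (20% v 50% and 30% v 60%): power 52% to 57% unadjusted, 59% to 68% adjusted.
- 30% success in both arms: type I error 3.8% and 2.3% unadjusted, 5.8% and 4.8% adjusted.

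Taking all runs together, the gain is about 2 to 4 points at 5% v 40%, about 3 to 7 at 10% v 45% (7.5 at the extreme in the table), and 6 to 14 for the 30-point effect. With non-prognostic factors the loss is about 1 to 2 points (86.7 − 85.7 = 1.0; 78.9 − 77.5 = 1.4).

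**3. If the additional regression is logistic.** With no responder in the control arm the treatment odds ratio is infinite. The chance of this among 22 controls is (1−p0)²²: 0.95²² = 32%, 0.90²² = 10%, 0.85²² = 3%. At 5% v 40% the expected number of responders is 22·(0.05+0.40) = 9.9, or 9.9/5 = 2.0 per parameter for treatment plus the four named covariates. In the first set of simulations such a model had no finite estimate in about 31% to 36% of trials at 5% v 40%, and in 8% to 12% at 10% v 45%. Adding PEG/tube and residence to an ordinary logistic fit raises the 5% v 40% figure to 35% to 52%.

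**The case against.** The case on the other side is substantial, and much of it stands.

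- **The test is valid.** A reader might infer that an unadjusted test after minimization gives false positives or bias. The simulations do not show this: type I error stays at or below nominal within simulation error. Some of the shortfall is not even due to the factors. With 5% success in both arms the chi-square test is at 1.5% when the factors are not prognostic, because the counts are so small, and the adjusted test is also low there (1.6% to 2.6%).
- **Omission is not established.** A reader might infer that PEG/tube and residence are left out of the regression. They are not named, but the list ends in *etc.* and so does not exclude them. What can be said is that only age is named and the list is open.
- **The logistic problem is conditional.** A reader might conclude that the regression is overfitted. The article gives neither the model type nor the control rate, and an unseen analysis plan may settle the form.
- **The two worst cases do not coincide.** It is tempting to put a large power gain beside a high risk of zero control responders. A 30-point effect has unadjusted power of about 77% at a 5% control rate and falls to 52% to 55% only at control rates of about 20% to 35%. At 30% the chance of no control responder is 0.70²² = 0.04%, with 22·(0.30+0.60) = 19.8 responders expected.
- **Prognostic strength is assumed.** Log-odds of 1.0 to 1.5 are odds ratios of 2.7 to 4.5 per level, and the article does not say that PEG/tube or residence predicts response.

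What remains is that the test of the primary proportion is stated in the article, and it does not use the factors on which the trial is balanced.

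**Conclusion.** The point holds as a question of efficiency and calibration. Allocation uses three factors, the stated primary test uses none of them, and the supporting regression names one. At 5% v 40%, the pair that reproduces 22 per group under the usual two-sided formula, little is lost: 2 to 4 points of power with strongly prognostic factors, nothing at log-odds of 0.5. The loss grows with a higher control rate or a smaller effect, which is also where the trial has least power to spare. The possible gain is larger than the possible cost of 1 to 2 points. All these sizes rest on assumed prevalences, prognostic strengths, control rates and a 0.8 biased coin; the direction does not depend on the exact values. The logistic part is a precaution for one possible model, not an error in the plan.

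**What to change.** 1. State the primary estimate and test as the difference in responder proportion between diet and usual care, from a linear regression of responder status on treatment, age band (three levels), PEG/tube and residential status. Take the confidence interval and p-value from a t distribution with the residual degrees of freedom. This stays estimable with no control responders.
2. Keep the unadjusted chi-square test as a supportive analysis.
3. In the additional regression, name all three minimization factors, close the covariate list, and state the model type. If the model is logistic, use a penalized (Firth) or exact fit; adding factors to an ordinary logistic fit would make the sparse-data problem worse.

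Cost: wording only, with no change to design, sample size or patient care, and about 1 to 2 points of power if the factors turn out not to be prognostic. The adjusted test was at 6.1% in one of the eight null settings tabulated, about two standard errors above 5%, so its calibration is worth confirming by simulation with the trial's actual minimization settings before the analysis is fixed.

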#### Prospective cost diary

The diary is used to identify all relevant cost aspects with respect to health care sector costs and patient and family costs [41]. Each diary covers a period of four weeks and will be filled out during the 4 week baseline period and during the 4 month study period. The intervention group will also fill out the diary during the 12 months of follow-up. Total costs will be estimated using a bottom-up approach, where information on each element of service used will be multiplied by an appropriate standardized unit cost and be summed to provide an overall total cost. For the cost valuation, standardized cost prices from the Dutch manual for cost analysis in health care research will be used [42].

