#### IIa) Trial-based economic evaluation

A baseline analysis will be performed to examine the comparability of groups at baseline for both costs and outcomes. If necessary, methods will be applied to control for differences in baseline [46]. A Kolmogorov-Smirnov test will be performed to investigate whether data are distributed normally. Despite the usual skewness in the distribution of costs, the arithmetic means will generally be considered the most appropriate measures for describing cost data [47,48]. Therefore, arithmetic means (and standard deviations) will be presented. In case the cost data are skewed, non-parametric bootstrapping will be used to test for statistical differences in costs between the intervention and usual care. The bootstrap replications will be used to calculate 95% confidence intervals around the costs (95% CI), based on the 2.5th and 97.5th percentiles. If cost data are distributed normally, t-tests will be used. The incremental cost effectiveness ratio (ICER) will be determined on the basis of the incremental costs and effects of the ketogenic diet in comparison with a waiting-list group. The cost-effectiveness ratio will be stated in terms of costs per outcome rate (decrease in seizure frequency and severity), and the cost-utility ratio will focus on the net cost per utility gained.

The robustness of the ICER will be checked by non-parametric bootstrapping. Bootstrap simulations will also be conducted in order to quantify the uncertainty around the ICER, yielding information about the joint distribution of cost and effect differences. The bootstrapped cost-effectiveness ratios will be plotted subsequently in a cost effectiveness plane. The choice of treatment depends on the maximum amount of money that society is prepared to pay for a gain in effectiveness, which is called the ceiling ratio. Therefore, the bootstrapped ICERs will also be depicted in a cost-effectiveness acceptability curve showing the probability that the ketogenic diet is cost-effective using a range of ceiling ratios. In addition, to demonstrate the robustness of our base-case findings, multi-way sensitivity analyses will be performed [49].

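### Continuous outcomes are tested mainly by t-test without the outcome's own baseline value as covariate, and economic baseline adjustment is conditional with no stated rule

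*Protocol article*

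**What the plan says.** **Effect evaluation (Analyses, I).** The main test is fixed: "between-group differences in means (continuous variables) will be tested using" an independent-samples Student's t-test. The text does not say whether the scores compared are T3 values or changes from T0. The next sentence adds: "In addition, a multivariate regression analysis will be performed with the covariates of sex, age, severity of disease, duration of disease etc". The covariate list is left open. It does not name the T0 value of the outcome under test.

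**Economic evaluation (Analyses, IIa).** The plan starts with an inspection: "A baseline analysis will be performed to examine the comparability of groups at baseline for both costs and outcomes". It continues: "If necessary, methods will be applied to control for differences in baseline", with a literature reference but no criterion in the text. Costs are then compared by bootstrap if skewed; otherwise, "If cost data are distributed normally, t-tests will be used".

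**Baseline data.** Table 1 schedules the seizure severity scale, the side-effect list, the EuroQol, the child quality-of-life scales and the cognitive and behavioural instruments at T0 and T3. Neither visit is marked as intervention group only. For costs, the Prospective cost diary section says: "Each diary covers a period of four weeks and will be filled out during the 4 week baseline period".

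**Randomization.** Minimization uses age band, PEG/tube and residential or outpatient status. Of these, only age is named as a regression covariate.

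**The concern.** The trial plans 22 evaluable children per arm, aged 1 to 18, and follows both arms for only four months before the controls also receive the diet. In a comparison that small, chance differences between the arms at T0 can be large relative to a plausible effect. If T3 scores are compared directly, part of any T0 difference carries into the result. If change scores are compared, the T0 value is subtracted in full, which over-corrects when the correlation is modest.

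Regression on the T0 value deals with both problems, using data that the trial already schedules. In the plan as written, that term is not named in even the supplementary model.

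On the economic side, whether to adjust is decided after looking at the baseline difference, in a trial where the researchers are not blinded. The QALY difference is the denominator of the cost-utility ratio, and cost-effectiveness is the distinctive aim of the study.

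**Working it through.** **Inputs from the protocol article.** 22 per group and alpha 5% (Sample Size; two-sided taken here); 4-month comparative period; T0 and T3 measurements in both arms (Table 1). The article gives no power figure for continuous or economic outcomes, so there is none to reproduce.

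**Assumptions, none given in the article.** True effect 0.6 SD; T0-T3 correlation r from 0.3 to 0.8; utility SD 0.25; simple randomization; equal SD at T0 and T3.

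**Step 1: power.** The variance of the comparison, relative to a t-test on T3 scores, is 2(1 - r) for change scores and 1 - r² for regression on the T0 value (ANCOVA). The standardized effect is 0.6 divided by the square root of that factor. Power comes from the noncentral t with noncentrality effect × √(22/2), on 42 df for the t-tests and 41 df for ANCOVA. For the t-test on T3 scores: 0.6 × √11 = 1.99, power 49% at every r.

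| r | Change scores: variance factor | Power | ANCOVA: variance factor | Power |
|---|---|---|---|---|
| 0.3 | 1.40 | 38% | 0.91 | 53% |
| 0.5 | 1.00 | 49% | 0.75 | 61% |
| 0.7 | 0.60 | 71% | 0.51 | 78% |
| 0.8 | 0.40 | 87% | 0.36 | 90% |

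The gain therefore depends on which t-test is meant. At r = 0.7 it is 49% to 78% against T3 scores, but 71% to 78% against change scores. At r = 0.3 it is 49% to 53% against T3 scores, and 38% to 53% against change scores. Against T3 scores at r = 0.7, ANCOVA with 22 per arm is worth 22/0.51 = 43 per arm.

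**Step 2: chance imbalance.** The SD of the baseline difference is √(2/22) = 0.30 SD units. A gap larger than 0.3 SD, in either direction, occurs in about 32% of trials of this size.

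**Step 3: QALYs over 4 months.** The SE of a chance difference in T0 utility is 0.25 × √(2/22) = 0.075. If it persists in full, it is worth 0.075 × 4/12 = 0.025 QALY. If it shrinks to r times its size by T3, with linear interpolation, multiply by (1 + r)/2: 0.025 × 0.85 = 0.021 at r = 0.7, and 0.025 × 0.75 = 0.019 at r = 0.5. For comparison, a true gain of 0.1 utility yields 0.1 × 4/12 = 0.033 QALY if immediate, or half of that, 0.017, if it builds up linearly.

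**Step 4: conditional adjustment.** No criterion is stated, so one possible reading was simulated: adjust only if a baseline t-test gives p < 0.05 (20,000 runs, 22 per arm, 0.65 SD effect, T3 scores otherwise).

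| r | Power, conditional rule | Power, always adjusted | Type I error, conditional rule |
|---|---|---|---|
| 0.5 | 56.5% | 67.2% | 4.3% |
| 0.7 | 57.2% | 82.8% | 3.7% |

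Under this reading the rule gives up most of the gain from adjustment. It does not inflate type I error.

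**The case against.** The strongest reply is that the plan may already use T0. The effect question in Research question I is about changes, and the trial-based economic evaluation refers to decreases in seizure frequency and severity. If the t-tests are on change scores, the loss at high correlation is small: 71% against 78% at r = 0.7, and 87% against 90% at r = 0.8. This stands, and it is why no single power loss can be quoted. It does not remove the point. The analysis section does not say which score is used, and change scores are less efficient than ANCOVA at every r in the table.

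Second, adjustment is planned. The covariate list is open-ended, so the T0 value is not excluded, and severity of disease might serve as the baseline value for seizure severity. That is fair, but the regression is supplementary, and severity of disease cannot play that role for cognition, behaviour, side effects or utility. The economic section also cites a method source that may contain a procedure, yet the wording still makes its use conditional.

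Third, minimization limits imbalance in age and whatever goes with it, so the simple-randomization standard errors above may be somewhat high. That too stands, although baseline utility, costs and seizure severity are not themselves minimized on.

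Three stronger readings are tempting, and the document does not support them:

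- A reader might infer that the t-tests are invalid or inflate false positives. They are valid under randomization.
- A reader might infer that the primary result is at risk. It is a responder proportion defined relative to baseline and is unaffected.
- A reader might infer that a baseline value exists on every instrument for every child. The Neurocognitive assessment section sets age floors (2 1/2 years for the vocabulary and Kaufman tests, 4 for the SDQ, about 6 for Fepsy) and says that some children are not testable. For those instruments the numbers fall below 22 per arm, and the power figures above do not apply as they stand.

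**Conclusion.** The point holds as a matter of efficiency and pre-specification for the secondary continuous outcomes and the economic evaluation. The main test leaves its score undefined and does not use the T0 value as a covariate. The economic adjustment has no stated trigger and follows a look at baseline differences.

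Under the stated assumptions, power forgone relative to baseline-adjusted regression runs from 4 points (r = 0.3) to 41 points (r = 0.8) if T3 scores are tested, and from 15 points (r = 0.3) to 3 points (r = 0.8) if change scores are tested. A chance utility imbalance of one standard error is about the size of the QALY gain from a 0.1 utility improvement. The effect size, the correlations and the utility SD are all assumed, so the ranges matter more than any single figure. The gaps in seizure severity, side effects, EuroQol and costs are the clearest, because baseline values are scheduled there in both arms without a stated testability limit.

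**What to change.** **Effect evaluation.** Make the main analysis of each continuous outcome a regression of the T3 value on arm, the T0 value of the same outcome, age group, PEG/tube and residence. For the cognitive and behavioural tests, state that it applies to children who are old enough and testable.

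**Economic evaluation.** Delete the condition on baseline adjustment. Always adjust QALYs for T0 utility and costs for baseline-diary costs, by regression within each bootstrap sample, so that the adjusted differences feed the ICER, the cost-effectiveness plane and the acceptability curve.

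**Cost.** Analysis wording only. No new data, visits or patients are needed.
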